### Outcomes

Primary outcome of our study is anxiety as measured by the anxiety-specific part of the CINT questionnaire. This scale relates to experienced anxiety on ICU and includes general anxiety, death related fear, fear of severe suffering, fear of a handicap, fear of the future, fear of uncertainty, panic, strain, depression, loneliness, lack of orientation, uncertainty and anger. All items are rated on a Likert-scale from 1 = never to 4 = always. This measure was specially developed for the reporting of ICU-related experiences and proved very useful in two previous studies [4,35,36].

Secondary outcomes of the study are:

• incidence of postoperative confusion (ICU-CAM) within the first 3 postoperative days

• postoperative state anxiety (STAI) on standard care ward

• postoperative complications, length of stay and McPeek Recovery Score at discharge

• state anxiety (STAI) 3 months follow-up

• quality of life and self-reported health state (SF-12) 3 months follow-up

• patient satisfaction with care and hospital (items from the Lübecker-Fragebogen-Doppelkarte) 3 months follow-up.

### Sample size calculation

Sample size calculation was performed with regard to the anxiety-specific part of the CINT questionnaire as the primary outcome. This score ranges between 0 and 100 with a standard deviation of SD = 17 [36]. Setting alpha at 0.05, beta at 0.20 and Δ = 8.50 (half a standard deviation as a clinically minimal relevant difference [56]) results in a required N = 100 (n = 50 patients in each group) [57]. In order to compensate for possible drop-outs that definitive number of patients to be included into this trial will be set at N = 120. This number relates to patients of the Department of Heart Surgery, a relatively homogenous group of patients.

In order to generalize findings over a wider group of patients, an additional N = 20 from the Department of Visceral, Thoracic and Vascular Surgery will be recruited.

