**Methods/Design:**

The trial is designed as a prospective randomized controlled trial including an intervention and a control group. The control group receives the standard preparation currently conducted by surgeons and anesthetists. The intervention group additionally receives a standardized information program with specific procedural, sensory and coping information about the ICU.

A measurable clinical relevant difference regarding anxiety will be expected after discharge from ICU. Power calculation (α = 0.05; β = 0.20; Δ = 8.50 score points) resulted in a required sample size of N = 120 cardiac surgical patients (n = 60 vs. n = 60). Furthermore, N = 20 abdominal or thoracic surgical patients will be recruited (n = 10 vs. n = 10) to gain insight to a possible generalization to other patient groups.

Additionally the moderating effect of specific patient attributes (need for cognition, high trait anxiety) will be investigated to identify certain patient groups which benefit most.

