### Data analysis

First of all the whole trial data will be analyzed using descriptive methods: mean, median, standard deviation, frequencies including graphical presentation. Statistical testing will be focused on the cardiac surgery group (n = 120; 60 vs. 60). The main hypothesis representing the primary outcome will be tested with a two-sided t-test for independent samples assuming; the level of statistical significance is set at alpha 0.05 (two-tailed). Secondary outcomes will be tested accordingly.

An important internal analysis will be the correlation of certain individual characteristics to measure which patients benefit more from the information program than others. Especially "need for cognition" and "APAIS" measured at baseline are expected to moderate the impact of the intervention program. This will be analyzed by comparing means of subgroups using the t-test and regression modeling. This is a new study question never investigated in research on preoperative information programs.

Statistical analyses will be performed on an intention to treat basis and will be supplemented using a per protocol approach. The smaller group of patients from the Department of Visceral, Thoracic and Vascular Surgery will be analyzed using descriptive statistics and the main purpose will be to see whether the distribution of crucial outcome parameters resembles the pattern of data found in the cardiac surgery patients.

All analyses will be performed using the SPSS for Windows software.

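### The required N = 100 does not give 80% power for the planned two-sided test; power is about 70% with 100 evaluable patients and about 78% with all 120

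*Protocol article*

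**What the plan says.** The Sample size calculation section of the protocol article bases the calculation on the anxiety part of the CINT questionnaire: "This score ranges between 0 and 100 with a standard deviation of SD = 17". The target difference is "half a standard deviation as a clinically minimal relevant difference", that is 8.5 points. The error rates are given without saying whether alpha is one-sided or two-sided: "Setting alpha at 0.05, beta at 0.20 and Δ = 8.50". The section then states that this "results in a required N = 100 (n = 50 patients in each group"). The step to the enrolment target follows: "In order to compensate for possible drop-outs that definitive number of patients to be included into this trial will be set at N = 120". No drop-out rate is given.

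The Data analysis section does fix the sidedness. The primary hypothesis is to be "tested with a two-sided t-test for independent samples", and "the level of statistical significance is set at alpha 0.05 (two-tailed"). Testing is confined to the cardiac group, 60 against 60; the 20 visceral, thoracic and vascular patients are only described.

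The Methods/Design part of the abstract says that the power calculation "resulted in a required sample size of N = 120 cardiac surgical patients", without mentioning the drop-out step.

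**The concern.** A standardised difference of 0.5, tested two-sided at 5% with 80% power, needs clearly more than 50 patients per group. The stated figure looks like the result for a one-sided alpha of 0.05, which is not the planned test. If so, the drop-out margin has been added to a number that was too low from the start, and the true type II error exceeds the stated 0.20.

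This is the only power statement for the primary hypothesis, and the article treats 8.5 points as the smallest difference that matters clinically. If the trial finds no significant difference, a reader who relies on the stated power would take this as stronger evidence against such an effect than the design can give.

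**Working it through.** **Inputs**

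- SD = 17, difference = 8.5, so d = 8.5/17 = 0.5 (Sample size calculation)
- alpha = 0.05, power = 1 − 0.20 = 0.80 (Sample size calculation)
- two-sided t-test for independent samples, equal groups (Data analysis)
- stated requirement: 50 per group; enrolment: 60 per group

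**Reproducing the stated figure**

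Normal approximation: n per group = 2(z_alpha + z_power)²/d².

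- One-sided 0.05: 2 × (1.645 + 0.842)²/0.25 = 49.5, so 50 per group. The noncentral t gives 50.15.
- Two-sided 0.05: 2 × (1.960 + 0.842)²/0.25 = 62.8, so 63 per group (N = 126). The noncentral t gives 63.8, so 64 per group (N = 128).

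The stated 50 per group therefore reproduces with a one-sided alpha of 0.05 (the same as a two-sided 0.10), and not with the planned test. The shortfall is 26 evaluable patients by the normal formula and 28 by the t-test.

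**Power at the planned numbers (d = 0.5, alpha 0.05)**

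| Per group | Two-sided, noncentral t | Two-sided, normal | One-sided, noncentral t |
|---|---|---|---|
| 50 | 69.7% | 70.5% | 79.9% |
| 60 | 77.5% | 78.2% | 86.0% |
| 64 | 80.2% | 80.7% | 87.9% |

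For the planned two-sided t-test, beta is 1 − 0.697 = 0.303 with 50 per group and 1 − 0.775 = 0.225 with 60 per group.

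**Difference detectable with 80% two-sided power**

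- 50 per group: d = 0.566, and 0.566 × 17 = 9.6 points
- 60 per group: d = 0.516, and 0.516 × 17 = 8.8 points

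**Drop-out step**

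Going from 100 to 120 implies an allowance of 20/120 = 16.7%. The same allowance applied to the two-sided requirement gives 128/(1 − 1/6) = 153.6, so 154 enrolled (152 when starting from 126).

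**The case against.** - **The one-sided origin is inferred.** The Sample size calculation section does not state sidedness, and the method it cites is not available here. The exact t calculation gives 50.15, which would round up to 51; only the normal approximation gives 50. This is fair, but the finding does not depend on how the number arose. It is too small for the only test that the article plans, by either formula.
- **The gap at full enrolment is small.** With 120 evaluable patients the shortfall is 2.5 percentage points, and it would vanish if the SD were about 16.5 (8.5/0.516) instead of 17. This is also true. But that case assumes no losses before the post-ICU questionnaire, while the article itself allows for 20. The material deficit is at the 100 evaluable patients that the calculation calls sufficient, and the 30% risk of a missed effect applies only if all 20 spare patients are lost.
- **The abstract is shorthand.** It gives the final enrolment, and the main text explains the step from 100 to 120. This makes the abstract a secondary point. Still, 120 was not the output of the calculation as the main text describes it, nor is it the two-sided answer.
- **Covariate adjustment could make up the loss.** It might help, but the planned test is unadjusted. The primary score is taken only after the ICU stay and has no baseline value. Reaching 80% would need a correlation between covariates and outcome of about 0.47 with 50 per group (1 − r² = 50/63.8) or 0.24 with 60 per group (1 − r² = 60/63.8). The article gives no such figure.

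**Conclusion.** The concern holds. With SD 17, a difference of 8.5 points and the two-sided 5% t-test of the Data analysis section, 80% power needs 64 evaluable patients per group, not 50. Power is 69.7% with 100 evaluable patients and 77.5% with 120. The type II risk thus lies between 22.5% (no losses) and 30% (20 losses), against the stated 20%. The drop-out margin does not close the gap even if nobody is lost.

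The result rests on the article's own SD and difference, equal groups and an unadjusted comparison. Only power is affected; the two-sided test still holds its 5% level.

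**What to change.** Keep 120 cardiac patients and the two-sided test, and correct the power statement in the Sample size calculation section and in the abstract. Suggested wording: *With two-sided alpha 0.05, a difference of 8.5 points and SD 17, 64 evaluable patients per group would be needed for 80% power. The planned 120 patients give about 78% power if none is lost and about 70% if 100 are evaluable; the difference detectable with 80% power is then 8.8 or 9.6 points respectively.* The abstract should no longer present 120 as the result of the power calculation.

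This costs wording only, but it gives up the stated beta of 0.20. If 80% power is to be kept with the same implied drop-out allowance, enrolment has to rise to about 154, which is 34 more cardiac patients. A prespecified adjustment for baseline covariates may recover some power without further recruitment, but the gain cannot be quantified from the article and should not be counted on in the power statement.

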### Drop-outs

Drop-outs will be documented thoroughly and included in data analysis to the point of drop-out. Sensitivity analysis will be undertaken assuming different models of outcome for the drop-outs.

### Data analysis

First of all the whole trial data will be analyzed using descriptive methods: mean, median, standard deviation, frequencies including graphical presentation. Statistical testing will be focused on the cardiac surgery group (n = 120; 60 vs. 60). The main hypothesis representing the primary outcome will be tested with a two-sided t-test for independent samples assuming; the level of statistical significance is set at alpha 0.05 (two-tailed). Secondary outcomes will be tested accordingly.

An important internal analysis will be the correlation of certain individual characteristics to measure which patients benefit more from the information program than others. Especially "need for cognition" and "APAIS" measured at baseline are expected to moderate the impact of the intervention program. This will be analyzed by comparing means of subgroups using the t-test and regression modeling. This is a new study question never investigated in research on preoperative information programs.

Statistical analyses will be performed on an intention to treat basis and will be supplemented using a per protocol approach. The smaller group of patients from the Department of Visceral, Thoracic and Vascular Surgery will be analyzed using descriptive statistics and the main purpose will be to see whether the distribution of crucial outcome parameters resembles the pattern of data found in the cardiac surgery patients.

All analyses will be performed using the SPSS for Windows software.

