### Measures

#### 1. Self-rated measures

The current emotional patient state is measured with the state-part of the German version of the State-Trait-Anxiety-Inventory (STAI) [34] after readmission to standard care (post-ICU) and 3 months after discharge. At the point of readmission to standard care unit, ICU-related experiences are assessed using the CINT, a scale specifically developed for these purposes and used in preliminary studies of our working group [4,35,36].

Furthermore, health-related quality of life is measured using SF-12 [37] at baseline and 3 months after discharge. Also 3 months post-discharge patient satisfaction is measured using selected items from the Lübecker-Fragebogen-Doppelkarte [38]. Further baseline characteristics that are relevant to our research questions and distinguish between different types of patients are: Trait-Anxiety-Scale [34], preoperative need for information with the Amsterdam Preoperative Anxiety and Information Scale (APAIS) [39], a modified version of the Need-for-Cognition-Scale (NC) [40-43] to measure individual differences in cognitive preoccupation, and finally subjective illness conceptions using assorted items of the Aachener Fragebogen zur Krankheitsattribution (AFKA_I) [44].

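### The planned comparisons are unadjusted t-tests although trait anxiety, APAIS and SF-12 are collected before allocation; a pre-specified ANCOVA would use them at almost no cost

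*Protocol article*

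**What the plan says.** All references are to the protocol article.

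- **Test.** Data analysis: "The main hypothesis representing the primary outcome will be tested with a two-sided t-test for independent samples", at a two-tailed alpha of 0.05. For the rest: "Secondary outcomes will be tested accordingly". Regression is named only for the question of which patients benefit more, not for the treatment comparison itself.
- **Baseline data.** Measures, 1. Self-rated measures: "health-related quality of life is measured using SF-12 [37] at baseline and 3 months after discharge". Trait anxiety and APAIS are also listed there as baseline characteristics. STAI state is listed only after return to standard care and at 3 months. CINT is listed only at return to standard care.
- **Timing.** Randomization: the envelope is opened once the baseline questionnaire is complete. Surgical department is the only stratification factor.
- **Sample size.** Sample size calculation: "This score ranges between 0 and 100 with a standard deviation of SD = 17", and "Setting alpha at 0.05, beta at 0.20 and Δ = 8.50" leads to 50 analysed per arm, with 60 per arm enrolled to cover drop-outs.

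**The concern.** The baseline scales are measured before allocation, so adjusting for them cannot introduce post-randomisation bias. A linear model with arm and baseline covariates targets the same mean difference as the t-test. If the covariates predict the outcome, its standard error is smaller. It also adjusts for whatever imbalance in anxious disposition arises by chance. Nothing in the design controls that imbalance within the cardiac group, which is the only group tested. With 50 per arm, the difference between arms in a baseline scale has a standard error of √(2/50) = 0.20 SD, while the target effect is 8.5/17 = 0.5 SD.

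The precision matters because the trial falls short of 80% power under its own two-sided test. For SF-12, a plain comparison of 3-month scores would leave the instrument's own baseline unused.

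**Working it through.** **Inputs.** Difference 8.5 and SD 17 (Sample size calculation); two-sided alpha 0.05 and independent-samples t-test (Data analysis); 50 per arm analysed as planned, or 60 per arm if every enrolled cardiac patient is analysed. The correlation r between covariates and outcome (with two covariates, the multiple correlation) is not in the documents and is varied from 0 upward.

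**Step 1: the plan's own figure.** By the normal approximation, n per arm = 2(z₁ + z₂)²(17/8.5)² = 8(z₁ + z₂)².
- Two-sided 0.05, power 0.80: 8(1.960 + 0.842)² = 62.8, so 63 per arm (N = 126). The t distribution gives 64 per arm (N = 128).
- One-sided 0.05, power 0.80: 8(1.645 + 0.842)² = 49.5, so 50 per arm (N = 100).

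The stated N = 100 is therefore reproduced only with a one-sided alpha of 0.05. With the two-sided test that the plan names, the noncentral t gives 69.7% power at 50 per arm and 77.5% at 60 per arm.

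**Step 2: effect of adjustment.** The residual SD is 17√(1 − r²), so the standardised effect becomes 0.5/√(1 − r²). Power is taken from the noncentral t with noncentrality [0.5/√(1 − r²)]·√(n/2).

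| Assumed r | Residual SD | Power, 50 per arm | Power, 60 per arm |
|---|---|---|---|
| 0 | 17.00 | 69.7% | 77.5% |
| 0.2 | 16.66 | 71.4% | 79.2% |
| 0.3 | 16.22 | 73.7% | 81.3% |
| 0.4 | 15.58 | 77.1% | 84.2% |
| 0.5 | 14.72 | 81.5% | 88.0% |

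Solving for 80% power gives r of about 0.47 at 50 per arm and about 0.25 at 60 per arm.

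**Step 3: the downside.** Charging two degrees of freedom at r = 0 and 50 per arm costs about 0.02 percentage points of power. The formula leaves out the slight variance inflation from chance covariate imbalance, which is also small with one or two covariates at this sample size.

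**Step 4: SF-12.** Let r be the correlation between baseline and 3 months, with equal variances σ² at both times. Then the variance per patient is:
- 3-month score alone: σ²
- change from baseline: 2σ²(1 − r)
- ANCOVA: σ²(1 − r²) = σ²(1 − r)(1 + r)

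Since 1 + r ≤ 2, ANCOVA is never worse than the other two. At an assumed r = 0.5 the three are σ², σ² and 0.75σ². A 25% reduction in variance is worth 1/0.75 = 1.33 times as many patients.

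**The case against.** **The t-test is not wrong.** In a randomised trial it is unbiased with the correct type I error. This stands: the point is about avoidable inefficiency, not an error in the plan.

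**A reader might infer that the baseline scales are strongly prognostic.** The documents do not support that. The self-rated measures section calls the scales relevant to the research questions and useful for distinguishing types of patient. The role given to trait anxiety (Abstract) and APAIS (Data analysis) is moderation of the effect. No correlation with CINT, STAI state or 3-month SF-12 is reported. CINT concerns the ICU stay itself and STAI state has no listed baseline score, so the case is weakest for the primary outcome.

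**A reader might also infer that ANCOVA would restore the missing power.** That does not follow either. At r = 0.2 the gain is under 2 points and power stays below 80% even at 60 per arm. The shortfall comes from the mismatch between the sample-size figure and the two-sided test. An unknown correlation is not a sound repair for that.

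**The SF-12 wording is condensed.** The sentence on secondary outcomes also covers the incidence of confusion and complications, which a t-test does not suit. It does not say whether SF-12 is compared as a 3-month score or as change. That the baseline is ignored is therefore an inference. What stands is that no adjusted comparison is stated, and ANCOVA is at least as precise as either reading.

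**The SAP may add an adjusted model.** Possibly, but the article itself fixes the primary test, so making ANCOVA primary changes a stated method. None of these objections counts against pre-specified adjustment; they limit how large a gain can be claimed.

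**Conclusion.** The point holds as a low-cost improvement to a valid analysis. It is clearest for 3-month SF-12 and reasonable, with less certain benefit, for CINT anxiety and STAI state. For the primary outcome the gain runs from nothing at r = 0 to about 12 percentage points at 50 per arm (69.7% to 81.5%) if r = 0.5. These figures rest on the protocol's difference and SD, and on values of r that are assumptions throughout. Adjustment may narrow the power shortfall but cannot be counted on to close it, and the sample-size statement needs its own correction.

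**What to change.** Before the allocation is revealed to the analyst, pre-specify:

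1. **SF-12 at 3 months:** ANCOVA on arm plus the corresponding baseline SF-12 score.
2. **CINT anxiety (primary) and STAI state at both times:** ANCOVA on arm plus baseline trait anxiety and APAIS, two-sided alpha 0.05.
3. **Reporting:** adjusted mean differences with 95% confidence intervals, with the unadjusted t-test as a supporting analysis.
4. **Sample size:** correct the statement separately for the two-sided test, without relying on an assumed correlation.

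Items 1 to 3 need no new data or patients, cost one or two degrees of freedom, and can be run in SPSS, the named software. Because the primary test is already stated in the protocol, the change should be documented as a dated amendment and not only as SAP wording. The planned concealment of allocation from the analyst until the final analysis allows this to be done credibly.

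### The 3-month STAI comparison is most naturally a stand-alone t-test that leaves unused the post-ICU score of patients lost by then; the cost is small and one mixed model removes it

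*Protocol article*

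**What the plan says.** All references are to the protocol article.

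- **Measures, 1. Self-rated measures:** the STAI state scale is given "after readmission to standard care (post-ICU) and 3 months after discharge". Only the trait scale is named at baseline, so the text gives two state scores per patient and no preoperative one.
- **Outcomes:** the two times are separate secondary outcomes, "postoperative state anxiety (STAI) on standard care ward" and "state anxiety (STAI) 3 months follow-up".
- **Data analysis:** the primary outcome is to be "tested with a two-sided t-test for independent samples" in the 120 cardiac patients, followed by "Secondary outcomes will be tested accordingly". No model that takes the two STAI scores together is named. The basis is intention to treat, with a per-protocol supplement, in SPSS.
- **Drop-outs:** patients who drop out are "included in data analysis to the point of drop-out", and sensitivity analyses under several outcome models are planned for them. Those models are not specified.

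**The concern.** A patient may complete the post-ICU STAI but not the 3-month form. In a pair of separate t-tests, that patient counts in the first comparison and is absent from the second. The post-ICU score says something about the missing 3-month score, because both come from the same scale in the same person, but the 3-month test cannot use it.

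Two things could follow. The 3-month comparison has less power than the collected data allow. And if return of the form depends on post-ICU anxiety, the patients compared at 3 months are a selected group, which can shift the estimated difference. What matters is how large either effect could be.

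**Working it through.** **Inputs from the article.** 60 per arm; two-sided alpha 0.05; a relevant difference of 0.5 SD (8.5/17, set for the CINT score and borrowed here for STAI). No drop-out rate is stated; going from 100 to 120 implies (120 − 100)/120 = 16.7%.

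**Assumptions not in the article.** Within-patient correlation ρ of 0.3, 0.5 or 0.7; loss at 3 months of 0, 10, 16.7 or 30%; a true effect of 0.5 SD at 3 months for the power figures.

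**The plan's own figure.** The article gives no power for STAI. Its only figure is 50 per group for CINT, from "Setting alpha at 0.05, beta at 0.20 and Δ = 8.50". With n per arm = 2(z_α + z_β)²/0.5²:
- two-sided: 2(1.960 + 0.842)²/0.25 = 62.8, so 63 per arm (126 in total);
- one-sided: 2(1.645 + 0.842)²/0.25 = 49.5, so 50 per arm (100 in total).

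The published 100 therefore matches a one-sided test, while Data analysis plans a two-sided one. That is a separate matter. The calculations below use the two-sided test.

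**Power when loss is unrelated to the score.** Let d be the fraction lost and n_obs = 60(1 − d). In SD units the t-test has variance 1/n_obs per arm. A joint model has (1 − ρ²)/n_obs + ρ²/60 = (1 − ρ²d)/n_obs, so its effective sample size is n_obs/(1 − ρ²d). Power = Φ(0.5·√(n/2) − 1.96).

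At d = 16.7%, n_obs = 50 and the t-test has Φ(2.50 − 1.96) = 70.5%. With ρ = 0.5 the variance ratio is 1 − 0.25 × 0.167 = 0.958, the effective n is 52.2 and power is 72.4%.

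| Loss at 3 months | t-test | Joint, ρ = 0.3 / 0.5 / 0.7 | Gain (points) |
|---|---|---|---|
| 0% | 78.2% | 78.2 / 78.2 / 78.2% | 0 |
| 10% | 73.8% | 74.2 / 74.9 / 75.9% | 0.4 to 2.1 |
| 16.7% | 70.5% | 71.2 / 72.4 / 74.2% | 0.7 to 3.7 |
| 30% | 63.0% | 64.2 / 66.4 / 69.9% | 1.2 to 6.9 |

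**Bias of the 3-month t-test when loss depends on the post-ICU score.** Simulation with 60 per arm, bivariate normal scores, and log-odds of loss changing by 1 per SD of post-ICU score (odds ratio about 2.7). The ranges cover ρ = 0.3 to 0.7.

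| How loss depends on the score | Bias, 16.7% loss | Bias, 30% loss | Type I error |
|---|---|---|---|
| Alike in both arms, no post-ICU effect | none | none | about 5% |
| Alike in both arms, 0.5 SD post-ICU effect | 0.01 to 0.03 SD | 0.02 to 0.05 SD | about 5% |
| In one arm only | 0.05 to 0.10 SD | 0.08 to 0.18 SD | 6 to 13% |
| Opposite in the two arms (extreme) | 0.09 to 0.20 SD | 0.15 to 0.36 SD | 7 to 38% |

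In the second row the loss percentage is that of the control arm; the intervention arm loses less (11.4% and 21.9%). The shift there is against the programme, so a true benefit is slightly understated. The joint estimate was unbiased within simulation error in every row.

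**Power in the second row.** A further simulation of 20,000 trials per setting, with a 0.5 SD effect at both times and 16.7% loss in the control arm, gave 69.3 / 68.5 / 67.4% for the t-test and 71.3 / 72.5 / 73.8% for the joint estimate (ρ = 0.3 / 0.5 / 0.7). The difference is about 2 to 6 points.

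**The case against.** A separate t-test for each of two listed outcomes is a valid randomised comparison, and with complete data the joint model returns the same 3-month contrast. The sentence on secondary outcomes is also shorthand. It cannot mean t-tests throughout, because incidence of confusion and complications are among those outcomes, and a fuller document may say more. This stands in part: two t-tests is the natural reading for a continuous scale, but it remains a reading.

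The figures also rest on a correlation and a 3-month loss that the article does not give. This stands, and is why ranges are shown. The 16.7% is an inferred allowance for a sample size set on the primary outcome, so loss at 3 months could differ.

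Two stronger readings are tempting and are not supported:

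- **That the t-tests contradict the Drop-outs section.** They do not. A patient lost before 3 months is used in the post-ICU comparison, which is what inclusion up to drop-out means. The section does not promise that earlier scores will inform later outcomes, and its sensitivity analyses already address selective loss. Whether they would use the post-ICU score cannot be told.
- **That the 3-month result will be materially biased, for instance towards no difference.** That needs missing forms and loss that depends on the post-ICU score. Where the dependence is the same in both arms, it also needs a post-ICU effect, and the shift is then small. Patients are unblinded and only one arm has the personal session, so return that differs by arm is conceivable, but nothing in the article indicates it.

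**Conclusion.** The point holds as a modest improvement to a secondary analysis; the planned tests are not invalid. Read naturally, the plan gives a 3-month STAI test that discards known post-ICU scores of patients lost by then. At the implied 16.7% loss and ρ of 0.3 to 0.7, this costs about 1 to 4 power points when loss is unrelated to the score, and about 2 to 6 when loss depends on it alike in both arms and the programme works at both times. In the latter setting the shift is about 0.01 to 0.05 SD across 16.7 to 30% loss, with type I error near 5%. Bias of about 0.05 SD or more, with inflated type I error, needs dependence that differs by arm. If all 3-month forms come back, nothing is lost. The primary CINT outcome is not affected.

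**What to change.** Analyse the two STAI state scores in one linear mixed model with arm, time and arm-by-time terms and an unstructured within-patient covariance, including every patient with at least one score. Report the arm difference with a 95% CI at each time from this model, and keep the two t-tests as supportive analyses.

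The cost is one model in place of two tests, in the software already named, with no new data or patients. The downside is that the model assumes missingness is explained by the observed scores. It does not correct loss that depends on the unseen 3-month score, so the sensitivity analyses in the Drop-outs section should stay and should cover 3-month STAI. The model also extrapolates implicitly to patients who die before 3 months, for whom a later anxiety score has no clear meaning; deaths should be reported separately by arm.

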## Discussion

A measurable, clinically relevant difference in the reduction of anxiety through a preoperative ICU-related information program is expected. Beyond that, interindividual differences in emotional and cognitive preoccupation will be considered that might moderate the impact of information programs and will allow to select patients that may profit most.

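### Subgroup t-tests and correlations cannot show who benefits more; the article also names regression but does not say that an arm-by-moderator term decides

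*Protocol article*

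**What the plan says.** The Data analysis section of the protocol article treats the search for patients who gain more as an important additional analysis. It names three tools. It first speaks of correlating individual characteristics. It then says that need for cognition and the APAIS "measured at baseline are expected to moderate the impact of the intervention program", and continues: "This will be analyzed by comparing means of subgroups using the t-test and regression modeling". It does not say whether the t-test compares arms inside a subgroup or subgroups with each other, how subgroups are formed, what terms the regression contains, or which of the three tools settles the question.

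The abstract (Methods/Design) states the aim with a different pair of characteristics: "need for cognition, high trait anxiety) will be investigated to identify certain patient groups which benefit most". The main Discussion says that the result "will allow to select patients that may profit most".

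**The concern.** Moderation means that the difference between arms changes with a baseline characteristic. The t-test wording can be read in two ways, and neither tests this:

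- **Arms compared inside each subgroup.** This gives one p-value per subgroup. Significance in one and not in the other is not evidence that the two effects differ.
- **Subgroups compared with each other.** This shows whether, for example, patients high in need for cognition score differently overall. That is a prognostic question.

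A simple correlation of a characteristic with the outcome is prognostic too. Of the three tools, only a regression with a product term addresses the question, and it stands beside methods that can give a different answer.

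What is at stake is the stated use of the result, which is to identify or select the patients who gain most. A chance split between subgroups could be taken as a reason to prefer some patients for a programme that helps all of them equally.

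**Working it through.** **Inputs from the documents.** SD and effect (Sample size calculation): "This score ranges between 0 and 100 with a standard deviation of SD = 17" and "Setting alpha at 0.05, beta at 0.20 and Δ = 8.50", so d = 8.5/17 = 0.5. Test level (Data analysis): "the level of statistical significance is set at alpha 0.05 (two-tailed". Patients: "required N = 100 (n = 50 patients in each group", with 60 per arm to be enrolled in the cardiac group.

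**Assumptions, not in the documents.** Each moderator is split at its median. The effect is the same 8.5 points in every patient. Moderation is claimed when exactly one half is significant.

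**The plan's own figure.** The article gives no figure for the moderation analysis. Its only calculation is for the primary test. The two-sided normal formula gives n = 2 × (1.96 + 0.8416)² × (17/8.5)² = 62.8, so 63 per arm (64 by noncentral t). The stated 50 per arm is not reproduced two-sided. It matches a one-sided 5% test: 2 × (1.645 + 0.8416)² × 4 = 49.5, so 50. That is a separate issue. Both 50 and 60 per arm are used below.

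**Step 1: power in each half.** Two-sided t-test with m patients per arm in the half, noncentrality 0.5 × √(m/2), 2m − 2 degrees of freedom.
- m = 25: power 0.410
- m = 30: power 0.478

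**Step 2: exactly one half significant when the effect is the same in both.** Probability 2p(1 − p).
- m = 25: 2 × 0.410 × 0.590 = 0.484 (simulated 0.482)
- m = 30: 2 × 0.478 × 0.522 = 0.499 (simulated 0.497)
- No effect at all: 2 × 0.05 × 0.95 = 0.095
- 25:75 split instead of the median, probability pₐ(1 − p_b) + p_b(1 − pₐ): 0.216 × 0.424 + 0.576 × 0.784 = 0.543 with 50 per arm, and 0.571 with 60 per arm

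**Step 3: the interaction test on the same simulated trials.** It rejects in 4.9% (50 per arm) and 5.0% (60 per arm).

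**Step 4: two independent moderators, simulated, uniform effect.** At least one split result appears in 65% (50 per arm) to 68% (60 per arm) of trials. At least one interaction test is significant in about 10%, with no correction for multiple testing.

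**Step 5: what the interaction test can detect.** For a difference in effect between halves, SE = 17 × √(4/m).

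| Per arm | m | SE | Difference for 80% power, 2.8016 × SE | Power for a difference of 8.5 |
|---|---|---|---|---|
| 50 | 25 | 6.8 | 19.1 | 24% |
| 60 | 30 | 6.2 | 17.4 | 28% |

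With the moderator kept continuous and 100 patients, SE = 17 × 2/√100 = 3.4 points per SD of the moderator, and 2.8 × 3.4 = 9.5 points per SD for 80% power. This is on a different scale from the 19 points between halves, so the two figures do not measure the loss from splitting.

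**The case against.** The strongest reply is that the sentence at issue also names regression. A regression with an arm-by-moderator product is the right analysis, and the preceding sentence speaks of characteristics that moderate the programme's effect. A journal article commonly leaves model terms to the full protocol or analysis plan, which is not shown. This stands. A reader might infer that the plan contains no valid test of moderation, and the document does not support that. It supports only that two unsuitable methods are named and that the interaction is not said to decide.

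A reader might also take the 48-50% as the plan's false-positive rate. The document states no decision rule and no cut-point, and does not say which means the t-test compares. The figure illustrates one way of reading the results and falls to 9.5% if the programme has no effect.

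On the moderators, it is tempting to say that the choice between trait anxiety and the APAIS is left open until the data are seen. The document does not say so. The Measures section lists all three scales as baseline measures, and the analysis section offers its pair as the leading examples, not as a closed list. The mismatch is real but minor.

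Finally, moderation is neither the primary nor a listed secondary outcome, and the Discussion is partly hedged. No passage plans to withhold the programme from anyone. This limits the severity. It does not make subgroup t-tests a test of moderation.

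**Conclusion.** The concern holds in limited form. Under either reading, the subgroup t-tests and simple correlations cannot show that the effect differs between patients, and the article does not make an arm-by-moderator term decisive. This conclusion needs no numerical assumption.

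The size depends on the assumed rule, the assumed median split, and a uniform 8.5-point effect with SD 17. Under these, a split result occurs in about half of trials, roughly ten times the 5% of an interaction test. The rate is high when the trial's own hypothesis is true and the programme helps everyone equally.

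The correct test is weak at this sample size. A difference in effect of 17 to 19 points between halves, at least twice the 8.5-point effect the trial is sized for, is needed for 80% power. The statement about selecting patients is therefore too confident whichever method is used. This should be fixed, but it does not touch the primary analysis.

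**What to change.** 1. Use one list of moderators in the abstract and the Data analysis section, settling whether trait anxiety, the APAIS or both stand beside need for cognition.
2. Replace the method sentence with wording such as: For each listed moderator, CINT anxiety will be regressed in the cardiac patients on arm, the moderator (continuous, centred) and their product. Any statement about moderation will rest only on the product coefficient and its 95% confidence interval. Subgroup means will be shown descriptively.
3. Label the analysis exploratory and state its low power.
4. Soften the Discussion, for example to say that the results may suggest which patients to study further.

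The cost is a change of wording and one regression per moderator in the planned software, with no new data. The downside is a more modest claim about what the trial can show on this question.
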